### Criteria for discontinuing or modifying allocated interventions {11b}

Patients randomized into the trial will be monitored via 8 internet-based tracking SRQs at 2, 4, 8, 13, 16, 26, 39, and 52 weeks after randomization regarding important changes in their symptomology and the need for communication with their primary care provider or implementation of a crisis management strategy (i.e., a participant expresses intent to harm themselves or others). Each tracking survey will contain questions assessing suicidality within the past 2 weeks. Participants who report thinking of suicide or death several times a day in some detail with at least some intent of acting on these thoughts will receive a closing statement at the end of their survey encouraging them to contact the National Suicide Prevention Lifeline ([name]) and/or online chat services (via https://suicidepreventionlifeline.org/). We will also provide the participant’s contact information to the National Suicide Prevention Lifeline for outreach, and we will generate a report to the participant’s primary care treatment provider. The Principal Investigator (PI) or designee will then notify the participant’s primary care treatment provider about the incident. The reviewing primary care treatment provider will then determine whether the participant should remain in the study. Other reasons for discontinuation from the study will be a patient’s need for hospitalization as assessed by their primary care treatment provider, clinically significant adverse events not consistent with continuation in the study as determined by the study team or the participant’s primary care treatment provider.

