**Methods:**

Enrolled patients (*n* = 3360) will be those who are beginning ADM-only treatment of MDD in primary care facilities throughout West Virginia, one of the poorest and most rural states in the country. Participating treatment providers and study staff at West Virginia University School of Medicine (WVU) will recruit patients and, after obtaining informed consent, administer a baseline self-report questionnaire (SRQ) and then randomize patients to 1 of 3 treatment arms with equal allocation: ADM only, ADM + self-guided i-CBT, and ADM + guided i-CBT. Follow-up SRQs will be administered 2, 4, 8, 13, 16, 26, 39, and 52 weeks after randomization. The trial has two primary objectives: to evaluate aggregate comparative treatment effects across the 3 arms and to estimate heterogeneity of treatment effects (HTE). The primary outcome will be episode remission based on a modified version of the patient-centered Remission from Depression Questionnaire (RDQ). The sample was powered to detect predictors of HTE that would increase the proportional remission rate by 20% by optimally assigning individuals as opposed to randomly assigning them into three treatment groups of equal size.

Aggregate comparative treatment effects will be estimated using intent-to-treat analysis methods. Cumulative inverse probability weights will be used to deal with loss to follow-up. A wide range of self-report predictors of MDD heterogeneity of treatment effects based on previous studies will be included in the baseline SRQ. A state-of-the-art ensemble machine learning method will be used to estimate HTE.

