## Data collection and management

### Plans for assessment and collection of outcomes {18a}

Assessments will be carried out with patient-reported SRQs augmented by EMRs that will provide information about relevant baseline information (e.g., information about treatment history prior to the intervention that might be relevant in predicting outcomes or HTE) as well as treatment information over the course of the trial involving both the ADM (type, dose, titration, switching, augmentation) and other treatments that might be relevant to outcome assignment among patients lost to follow-up in the SRQ assessments (e.g., psychiatric hospitalizations, emergency department visits for mental health crises, suicide attempts, suicide deaths, other deaths by external cause). Additionally, assessments will be gathered via smartphone with consenting participants capturing ecological momentary assessments as well as sensor data from the smartphone app mindLAMP [82, 83] that can be used to derive estimations for daily physical activity, sedentary activity, sleep duration, screen time exposure, and social behaviors. Participants will be asked to download an Apple or Android version of mindLAMP onto their personal smartphones for these measures.

The SRQs will be collected remotely by a health survey firm that has extensive experience implementing mixed-mode web-phone surveys. Computerized procedures will be used to automate skip logic, flag missing values for completion, disallow out-of-range and inconsistent responses, and discourage superficial responses. This survey firm will also carry out the telephone interviews with SRQ nonrespondents. Each SRQ will be sent by email. Reminders to initial nonrespondents will be sent 3 and 6 days later. Options will be provided for participants who want to break up an SRQ for completion over multiple sessions. Telephone follow-up calls and interviews with initial SRQ nonrespondents will be carried out by the survey firm in conjunction with the SRQs at 2, 16, 26, and 52 weeks. The survey firm will also maintain an 800 number for technical assistance.

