### Interim analyses {21b}

Interim analyses will be conducted only to assess patterns and predictors of attrition for purposes of improving the targeting of motivational interviewing contacts to improve intervention uptake and continued engagement. Ongoing data monitoring will also be used if requested by the Data Safety Monitoring Board to facilitate recommending changes to study activities. Attending clinicians will be notified when reports of suicide thoughts or behaviors are reported and will inform study staff if there is a recommendation to discontinue study activities. Participants who report acute suicidal thoughts or behaviors will be flagged for follow-up. The study team will inform the participant’s treatment provider when there is a patient-reported suicide attempt or ideation with a plan and intent.

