### Composition of the data monitoring committee, its role and reporting structure {21a}

The PI along with co-investigators will have overall responsibility for monitoring the integrity of study data and participant safety. In addition, an independent monitoring committee, the Data and Safety Monitoring Board (DSMB), will be established. DSMB members will consist of (1) an expert in mental health research; (2) a clinical researcher experienced in conducting randomized clinical trials for depression; (3) three experts in assessing and treating depression; and (4) a stakeholder with immediate family members diagnosed with mood disorders. All members of the DSMB will either be established PIs, have DSMB experience, lived experience with mood disorders, and/or will be intimately familiar with the safety and ethical concerns related to human subjects in clinical research. The DSMB will review the progress of the trial and safety of participants bi-annually (i.e., two times per year), discuss any safety concerns that have arisen, and make recommendations to improve safety procedures if indicated. At each meeting, the DSMB will evaluate the progress of this project, review data quality, recruitment, and study retention and examine other factors that may affect outcome. The DSMB will review reports of any serious adverse events and/or unanticipated problems that occurred within the past study period. They will review the rates of adverse events to determine any changes in participant risk. The chair of the DSMB will report back to the AMHI investigators and will generate a brief report regarding each meeting for the study record and forwarded for review to the Institutional Review Board (IRB).

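### The follow-up suicidality items look back 2 weeks and so cover 16 of 52 weeks; attempts outside those windows depend on looser routes that may be incomplete and may differ by arm

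*Protocol article*

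**What the plan says.** The section on discontinuing or modifying interventions {11b} has randomized patients "monitored via 8 internet-based tracking SRQs at 2, 4, 8, 13, 16, 26, 39, and 52 weeks after randomization", and adds: "Each tracking survey will contain questions assessing suicidality within the past 2 weeks". A report of frequent, detailed thoughts with some intent leads to a crisis-line message, outreach and a report to the primary care provider. Table 6, which lists what the follow-up questionnaires measure, has no row for suicidal behaviour.

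Other sections rely on reports of discrete events:
- Interim analyses {21b} has the study team inform the provider "when there is a patient-reported suicide attempt or ideation with a plan and intent".
- Adverse event reporting {22} counts a recent attempt among the anticipated adverse events.
- The monitoring committee section {21a} says of the board: "They will review the rates of adverse events to determine any changes in participant risk".

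The article also gives other routes by which an attempt can become known:
- Section {22} provides a continually monitored 800 number, asks for adverse-event reports when participants are contacted about questionnaires, and obliges coaches and telephone interviewers to pass on what they hear.
- Outcome collection {18a} draws on medical records for "psychiatric hospitalizations, emergency department visits for mental health crises, suicide attempts, suicide deaths, other deaths by external cause".
- Telephone interviews of web nonrespondents take place only "in conjunction with the SRQs at 2, 16, 26, and 52 weeks".

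**The concern.** A 2-week look-back suits current ideation, where the purpose is to act on present risk. An attempt is different: it is a discrete event that matters for safety whenever it happened. The questionnaires are 2, 2, 4, 5, 3, 10, 13 and 13 weeks apart, so the longest uncovered stretches come late in the year. Someone who attempts suicide at week 20 or week 30 could truthfully answer no to a 2-week item at every later questionnaire.

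What is at stake is the quality of the attempt rates used for safety monitoring in a depression trial of 3360 patients. If the structured items see less than a third of follow-up, the rest depends on routes that are less uniform. At least one of those routes exists in a single arm.

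**Working it through.** The article states no coverage figure, so there is none to reproduce.

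**Inputs**
- Questionnaire weeks 2, 4, 8, 13, 16, 26, 39 and 52, from {11b} and the abstract.
- A look-back of 2 weeks, from {11b}.
- Follow-up of 52 weeks, of which 52 − 16 = 36 fall after the week-16 primary time point.
- Telephone interviews at weeks 2, 16, 26 and 52, from {18a}.

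**Formula.** Covered time is the union of the intervals [t − 2, t] over the questionnaire weeks t, divided by the length of the period.

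**Windows.** [0,2], [2,4], [6,8], [11,13], [14,16], [24,26], [37,39], [50,52]. None overlap, so the union is 8 × 2 = 16 weeks.

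| Period | Covered | Not covered |
|---|---|---|
| Weeks 0–52 | 16/52 = 30.8% | 36/52 = 69.2% |
| Weeks 0–16 | 10/16 = 62.5% | 6/16 = 37.5% |
| Weeks 16–52 | 6/36 = 16.7% | 30/36 = 83.3% |
| Weeks 0–52, reached only at the four telephone waves | 8/52 = 15.4% | 44/52 = 84.6% |

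**Cross-check.** The gaps are weeks 4–6, 8–11, 13–14, 16–24, 26–37 and 39–50, that is 2 + 3 + 1 + 8 + 11 + 11 = 36 weeks. This agrees with 52 − 16.

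The first three rows assume that every questionnaire is completed, so they are upper limits on coverage. The sample-size section itself assumes 30% loss to follow-up.

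**What the other routes add**

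| Route | In all arms? | Limit, as described |
|---|---|---|
| Request for adverse-event reports at questionnaire contacts {22} | Yes | General; no recall period or attempt question given |
| 800 number {22} | Yes | Relies on the participant to call |
| Medical records {18a}, {19} | Yes, if the participant consents | Described for prediction, treatment tracking and outcome assignment among those lost to follow-up; no stated path to the adverse-event log; misses attempts without medical contact |
| Telephone interviewers {18a}, {22} | Yes | Nonrespondents only, at four waves |
| Coaches {22} | No, guided arm only | An extra reporting route in one arm of three |

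**After the change.** If recall runs back to the previous questionnaire (longest interval 13 weeks), the same eight surveys cover 2 + 2 + 4 + 5 + 3 + 10 + 13 + 13 = 52 of 52 weeks when all are completed.

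**The case against.** The strongest reply is that the 2-week items were never meant to count attempts. They sit under discontinuation criteria, and the trigger described is current ideation with intent. The article does not say that attempts are asked about only within that window, and {21b} mentions patient-reported attempts without any recall limit. Section {22} seeks adverse-event reports at questionnaire contacts, which every arm has, and {18a} names suicide attempts and deaths among the record data. No section says that the board's rates come from the 2-week items. The exact questionnaire wording and the data safety and monitoring plan are not shown, and suicidal behaviour is not a primary or secondary outcome.

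Most of this stands. It rules out several stronger readings that a reader might take from the percentages:
- That attempts in the gaps go unreported. The article gives several routes by which they could be reported.
- That the 2-week items are the only systematic source common to all arms. The request for adverse events at questionnaire contacts is also common to all arms.
- That the questionnaires miss 69% of attempts. This would need attempts spread evenly over time, attempts asked about only with the 2-week window, and nothing gained from the general request.
- That the board will see a falsely low rate. The documents do not show which source feeds its rates.

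The reply does not remove the narrower point. Each alternative route is unstructured, passive, dependent on consent or confined to one arm, and the only recall period the article states for suicidality is 2 weeks.

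**Conclusion.** The point holds as a risk to safety ascertainment, with a cheap remedy; it is not an error in a stated figure or a contradiction between sections. The specified suicidality items cover at most 31% of the follow-up year and 17% of the time after week 16. Outside those windows, capture of attempts depends on routes that may be incomplete. Because coaches add a route in the guided arm alone, capture may also be unequal between arms.

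The coverage figures rest only on the stated schedule and look-back, and assume full response. How many attempts would actually be missed cannot be derived from the article, and no undercount is demonstrated. If the full questionnaire or the safety plan already contains an attempt item with a longer recall, the point reduces to stating that in the article.

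**What to change.** Keep the 2-week window for current ideation and leave the crisis procedure as it is. Add to each follow-up questionnaire, in the same words in all three arms, an item on suicide attempt or self-harm and one on psychiatric hospitalization or emergency visit. Each should refer to the time since the last completed survey, or since randomization when first asked. The reference date can be filled in automatically from the last completed survey, so a missed wave is recovered at the next one completed. Use the same items in the telephone interviews.

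Tabulate the answers by arm for the Data and Safety Monitoring Board, separately from events learned through coaches, the 800 number or records, so that the comparison rests on a source collected alike in every arm. State the recall period for the general adverse-event request as well.

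The cost is one or two items per survey, some programming and a minor amendment, with no added visits or staff. Dating becomes less precise over recall of 10 to 13 weeks. Events after a participant's last completed survey would still depend on the other routes.

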### Strategies to improve adherence to the interventions {11c}

i-CBT users often exhibit low levels of engagement, especially in disadvantaged populations [59]. We will address this problem using several strategies. First, patients assigned to i-CBT will both be (i) sent email messages notifying them of these assignments and (ii) receive a phone call from study staff using motivational interviewing techniques to encourage engagement [60]. Second, the first two brief SRQs, at 2 and 4 weeks after randomization, will be used as additional occasions to monitor intervention engagement. Patients that either fail to respond or (in the case of the i-CBT arms) report that they have not yet started the intervention will receive additional motivational interviewing contacts to encourage engagement with the assessments and (in the i-CBT arms) the interventions. Consistent with previous research [61, 62], we anticipate that these frequent contacts will increase engagement. Third, we will attempt to build on a recent process analyses of meta-data from over 50,000 SilverCloud users, which identified five early longitudinal user engagement profiles that predict treatment response [63]. To the extent possible, we will score these clusters for each patient assigned to SilverCloud and use the profile scores to target the subset of patients identified as non-engagers in weeks 3–4 of the trial for additional motivational outreach email messages.

### Relevant concomitant care permitted or prohibited during the trial {11d}

Eligible patients will be treated for major depression by their primary care physician. We will not control type or dose of ADM prescribed, but we will track dose, titration, augmentation, and switching through EMRs. Some patients will also be treated with other psychotropic medications for comorbid conditions, such as anxiolytics for comorbid anxiety disorders, stimulants for ADHD, or addiction medications for comorbid substance use disorders, and these will be allowed. However, patients treated with anti-mania medications or antipsychotics will be ineligible for the trial due to the exclusion of patients with a history of bipolar disorder or psychosis.

### Provision for post-trial care {30}

Access to SilverCloud will continue for 12 months after randomization for patients randomized to the two i-CBT arms.

### Outcomes {12}

The primary outcome will be MDD remission at 16 weeks as defined by a revised version of the composite patient-centered Remission from Depression Questionnaire (RDQ) [64, 65]. The RDQ is a patient self-report scale that assesses the 7 dimensions found in extensive research to be the ones most important to patient-centered definitions of MDD recovery: [66–68] remission from depressive and non-depressive (e.g., anxiety) symptoms, positive mental health, coping ability, productive and social role functioning, life satisfaction, and global sense of well-being. The RDQ is the best validated patient-reported outcome measure of these 7 dimensions. It has excellent psychometric properties, is as sensitive to change as symptom-based scales, but captures additional information [64, 69]. Importantly, patients consistently say that the RDQ represents their treatment goals more than standard symptom scales [70]. Based on evidence of a strong second-order factor across the 7 RDQ dimensions [64], an aggregate score can also be derived. Our primary outcome will be a dichotomous definition of remission based on this aggregate score at 16 weeks and of maintenance of remission at 26, 39, and 52 weeks. The cutoff for this designation in the RDQ was calibrated by the RDQ developers to balance false positives and false negatives in using composite RDQ scores to predict patient reports of “being completely back to normal.” This calibration exercise will be replicated in AMHI to guarantee the internal validity of results. In addition, the depression symptom severity scale used in AMHI will be different from the one in the RDQ: the Quick Inventory of Depressive Symptomatology Self-Report (QIDS-SR) [71]. The QIDS-SR will be used because of its strong association with the gold standard Hamilton Rating Scale for Depression (HRSD) [72] and the existence of a validated crosswalk between the QIDS-SR and HRSD [73]. The focus on a dichotomous measure of remission as the primary outcome is based on evidence that MDD remission is critical for reducing recurrence, leading treatment guidelines to call for MDD to be treated to remission [35, 74]. The 7 dimensional RDQ and QIDS-SR scores will be secondary outcomes. Given the prominence of substance use disorders in West Virginia [75] and the high comorbidity of MDD with these disorders in the population [76], we will also include a substance use disorder symptom scale [77] as a secondary outcome. Anxiety comorbidity, while also of interest, is already addressed in one of the RDQ dimensions. Finally, a measure of ADM treatment compliance based on EMR data, measures of treatment engagement based on both self-reports and administrative records [78], and a patient-reported measure of shared decision-making [79] will be additional secondary outcomes.

### Participant timeline {13}

The participant timeline is outlined in Fig. 1. Potential study participants identified at participating clinics during their initial visit will be informed of the study by their treatment provider. Additionally, they will be provided with a study fact brochure, which contains highlighted study information as well as the study website URL and an 800 number for additional questions. Participating clinics will then gain permission from their potentially eligible participants to provide AMHI study staff with their contact information for enrollment. Potentially eligible patients who were not informed of the study during their initial treatment visit will be sent a letter with the signature of their treatment provider along with the study fact brochure explaining the study and informing these patients that a study staff member will call to further explain the study and discuss possible enrollment. The letter will also include the study 800 number for patients that want more information or to opt out. AMHI study staff at WVU will then contact, gain informed consent, and subsequently enroll each participant into the study. Upon receipt of informed consent, potentially eligible participants will be emailed a link to complete the baseline SRQ and an online web challenge to evaluate cognitive performance. Given the nature of eligibility criteria, a final decision about eligibility will be made only after completion of the baseline SRQ and online web challenge. Eligible participants will then be randomized to one of the three treatment arms. The finite selection model will be used to increase balance in baseline covariates across treatment arms [46]. Email will be used to notify patients of these assignments. Participants in the i-CBT arms will then receive a phone call from study staff using motivational interviewing techniques to encourage engagement with the intervention [55]. Regardless of the arm the participant is randomized to, subsequent SRQs will then be administered at 2, 4, 8, 13, 16, 26, 39, and 52 weeks post randomization. Participants that fail to complete SRQs will receive a set of reminder emails encouraging completion. Additionally, participants that fail to complete SRQs in weeks 2, 16, 26, and 52 will receive phone calls using motivational interviewing techniques to complete SRQs.

